#### Measurements

We will extract baseline demographics and health survey data, 12-monthly TAS Test data, and CANTAB tests at baseline, + 24, and + 48 months.

### Sample size

#### Aim 1

We estimate that 17% (or 85 individuals) in the cognitively unimpaired THBP & HBA cohorts will have p-tau181 in the preclinical AD range [45]. We have performed ROC curve analysis using open data from Mollica et al. [19]. This showed area under ROC curve (AUC) of 0.75 for a null linear model including age, sex, ApoE4, and years of education, but not finger tapping, to detect p-tau181 positivity in CSF. To develop the multivariable model, power calculation showed the sample size to compare a screening test with an area under the curve (AUC) > 0.90 against the null model would require 60 positive p-tau181 cases and 290 controls. Thus, we will use 350 in the development dataset (expected 60 [17%] preclinical AD cases) and 150 in the validation dataset (expected 25 [17%] preclinical AD cases) to test cut-offs from the development model. The PROBAST tool [46] confirmed these combined development and validation strategies lower the risk of bias.

#### Aim 2

Based on the age distribution of ISLAND participants, we project that 8.6% of participants currently aged 70–74 years (a cohort of ~ 1300 from the 10,000 recruited) will develop dementia, and more than 16% of the 700 participants currently aged 75+ years will develop dementia over the study duration [47, 48]. Thus at least 200 participants will meet diagnostic criteria for dementia or MCI. Our sample size calculation aims to ensure precise estimation of model parameters while minimising potential of overfitting. A sample of 300 including 100 dementia cases would ensure accurate prediction of the outcome proportion (33%) with a targeted confidence interval of 28–38%. To target a mean absolute prediction error (MAPE) < 0.05, as recommended by Riley et al. [49], a sample of 300 would be adequate for up to 6 predictors in a parsimonious, statistically determined risk prediction model.

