**Discussion:**

This study will establish the precision of TAS Test to identify preclinical AD and estimate risk of cognitive decline and AD. If accurate, TAS Test will provide a low-cost, accessible enrichment strategy to pre-screen individuals for their likelihood of AD pathology prior to more expensive tests such as blood or imaging biomarkers. This would have wide applications in public health initiatives and clinical trials.

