### Further data collected

Data will also be collected on age, sex, years of education, English as first language, dominant hand, motor and cognitive symptoms, levels of pain and anxiety, and neurological diagnoses (Supplementary file 1). The following passive data will be collected without user input: log in time, log out time, user’s real-time mouse track, click actions on website internet browser (Chrome/Firefox/Safari etc). By collecting times of start/stop button clicking, we can understand how participants behave when they are using the application. For example, if a participant clicks start and stop several times, this means that the recording process may be difficult for participants to use. Time of day may influence performance. The following system-related data will be collected: Internet Protocol Version 4 (IPV4) address, browser information (name, version, product, manufacturer, layout), operating system, computer screen resolution, webcam information (resolution and frame rate). By collecting system information, such as browser information (version, product, manufacturer, layout), operating system (version, platform), camera resolution, video upload time, we can evaluate how different system environments may affect application administration.

### Aim 2

To validate TAS Test to prospectively estimate 5-year risks of cognitive decline and AD.

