### Statistical analysis

#### Aim 1

To develop the TAS test protocol and validate it against p-tau181, data from 350 participants with no cognitive impairment will develop the model. Data from the remaining 150 participants in this validation dataset will determine the model’s sensitivity and specificity in detecting preclinical AD. Replicates of plasma biomarkers will be assessed for outliers and then averaged. Hand-movement data will be summarised for each participant. Participants with unimpaired cognition and mean p-tau181 above a diagnostic cut off will be classified as ‘preclinical AD’. We will use multiple logistic regression to model the associations between movement features and p-tau181 positivity. Covariates may include age, sex, ApoE4 genotype, years of education, and handedness. As a secondary, more agnostic approach, we will use a deep learning approach to discover features in the video and keyboard movement data that map to p-tau181 positivity. To validate the TAS Test multivariable model, we will use cross-validation for model selection to avoid overfitting and bootstrap procedures to estimate model uncertainty. We will independently validate the model using the remaining 150 participants’ data. Receiver Operating Characteristic (ROC) curves will be plotted against the positive p-tau181 cut-off to assess the sensitivity and specificity of movement models to identify the preclinical AD stage. As TAS Test is intended as a screening test, the resulting curves will allow users to make informed choices about sensitivity and specificity that align with their research or health promotion goals.

#### Aim 2

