To validate prospectively against cognitive decline, we will assess the sensitivity and specificity of TAS Test to predict cognitive trajectories (“stable” and “declining”) using ROC curve analysis. We will estimate 5-year cognitive decline/MCI/AD risk using baseline TAS Test data in a sub-sample of 300 people. Clinical diagnostic categories are: cognitively unimpaired, MCI, and AD. Covariates considered in the model will include age, sex, ApoE4, years of education, and handedness. We will use Bayesian multinomial logistic regression with regularizing priors to estimate the covariate adjusted log-odds of being in each diagnostic category at 5 years as predicted by baseline TAS Test results. The resulting prediction model will estimate posterior highest density intervals for 5-year risk of conversion to MCI and AD using TAS Test results. There is a risk that not all participants classified as MCI will have prodromal AD (as MCI is a heterogeneous group with a variety of causes) but to account for this, we will perform post-hoc analyses of sub-groups with indicators of higher risk, for example, amnestic sub-type of MCI, p-tau181 positive, ApoE4, longitudinal cognitive decline. Data analysis and statistics will be performed in consultation with a biostatistician.

*Descriptive statistics*: The quantitative variables will be described using mean, standard deviation (SD) and range, or median and inter-quartile range if not normally distributed; Qualitative variables will be described using frequency and percentages.

*Test-retest reliability* will be assessed between the first and second completions of TAS Test at home (12 months), and between completions in the research centre and the home (3–6 months). Stability of the TAS Test assessments will be analysed by measuring the intra-class correlation coefficient and by use of Cohen’s kappa coefficient of agreement.

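### ApoE4 genotype is allowed in the models behind TAS Test's accuracy and 5-year risks, although a home pre-screen used before blood tests does not collect it

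*Protocol article*

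**What the plan says.** **Intended use.** The Discussion part of the Abstract says that TAS Test could "pre-screen individuals for their likelihood of AD pathology prior to more expensive tests such as blood or imaging biomarkers". The Background repeats this: a test done at home without specialist supervision, ahead of blood biomarkers where those exist.

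**What is collected online.** Under Further data collected: "Data will also be collected on age, sex, years of education, English as first language, dominant hand", followed by symptoms, pain, anxiety, neurological diagnoses, and passive and system data. Genotype is not listed.

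**Where ApoE4 comes from.** In the Aim 2 cohort it comes from blood samples, held for about 2,000 participants when over 13,500 had been recruited, or from the clinic work-up of the 300 (Aim 2, Participants). For Aim 1, the Participants section says only that the Tasmanian cohort had genetic tests at baseline.

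**Aim 1 model (Statistical analysis).** "Covariates may include age, sex, ApoE4 genotype, years of education, and handedness". The 150 validation participants then give this multivariable model's sensitivity and specificity, and under Sample size they test the cut-offs from the development model.

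**Aim 2 model (Statistical analysis).** "Covariates considered in the model will include age, sex, ApoE4, years of education, and handedness". This is the multinomial model that yields the 5-year risks of MCI and AD.

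**Planning comparator (Sample size, Aim 1).** "This showed area under ROC curve (AUC) of 0.75 for a null linear model including age, sex, ApoE4, and years of education". The aim is to "compare a screening test with an area under the curve (AUC) > 0.90 against the null model".

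**The concern.** A model with a genotype term cannot be run by the person for whom the test is designed, and its cut-offs do not apply to someone with no genotype. If ApoE4 carries information about p-tau181 status or later diagnosis, a model that keeps it will discriminate better than the online test can alone. The claim that a low-cost test needing no blood sample detects preclinical AD, or predicts decline, could then rest on a model that needs a genotype.

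The wording for Aim 1 is permissive, so the choice can be made after the data are seen. For Aim 2, the output is described as risk from TAS Test results although the model behind it may carry the genotype. The Aim 1 section says that the ROC curves will let users choose their own balance of sensitivity and specificity. That works only if the curves describe a test those users can take.

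**Working it through.** **1. The plan's own figure.** The plan states that the comparison "would require 60 positive p-tau181 cases and 290 controls". Error rate, power and correlation between the two ROC curves are not given; I assume two-sided 5%, 80% power and independent curves.

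- Obuchowski variance: V(A) = 0.0099·exp(−a²/2)·[(5a²+8) + (a²+8)/k], with a = 1.414·Φ⁻¹(A) and k = 290/60 = 4.83.
- V(0.90) = 0.0513 and V(0.75) = 0.0904.
- Cases = [1.96·√(2·0.0904) + 0.84·√(0.0904+0.0513)]² / 0.15² = 58.8, so 59 cases and about 285 controls.

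The stated size is reproduced closely.

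**2. Which way does ApoE4 act in the comparator?** It can only raise the null AUC, which makes the gap to 0.90 smaller and harder to show. With the Hanley–McNeil variance under the null and the same assumptions, 57 cases are needed at a null AUC of 0.75 and 35 at 0.70. ApoE4 in the comparator is therefore a stricter benchmark and does not flatter TAS Test. Any overstatement comes from ApoE4 in the model being evaluated.

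**3. How large could the overstatement be?** The documents give no AUC for ApoE4 alone, so I assume 0.55 to 0.70. The model is equal-variance binormal with independent contributions:

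- d′ = √2·Φ⁻¹(AUC)
- d′²(without ApoE4) = d′²(full) − d′²(ApoE4 alone)
- AUC = Φ(d′/√2)
- sensitivity at 80% specificity = Φ(d′ − 0.8416)

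For the plan's target of 0.90, d′ = 1.812, d′² = 3.285, and sensitivity = Φ(0.971) = 83.4%.

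| Assumed ApoE4-alone AUC | d′² of ApoE4 | d′² left | AUC without ApoE4 | Sensitivity at 80% specificity |
|---|---|---|---|---|
| 0.55 | 0.032 | 3.253 | 0.899 | 83.2% |
| 0.60 | 0.128 | 3.156 | 0.895 | 82.5% |
| 0.65 | 0.297 | 2.988 | 0.889 | 81.2% |
| 0.70 | 0.550 | 2.735 | 0.879 | 79.2% |

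The loss is 0.001 to 0.021 in AUC and 0.2 to 4.2 points in sensitivity.

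**4. Does the text settle which model gives the headline figures?** The Aim 1 section speaks of ROC curves for movement models. It also assigns the validation sensitivity and specificity to the multivariable model, whose covariates may include ApoE4. The Aim 2 trajectory ROC is of TAS Test with no covariates named, so it is not clearly affected. The Aim 2 multinomial model is covariate adjusted, with ApoE4 among the candidates. Neither section commits to an estimate without genotype.

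**The case against.** The strongest reply is that the plan does not commit to a genotype term. ApoE4 is optional in Aim 1 and only a candidate in Aim 2. The deep-learning analysis uses video and keyboard data only, and the ROC analyses are described as those of movement models and of TAS Test. An article may also leave the final covariate set to a fuller document. This stands to the extent that the overstatement is conditional on ApoE4 being kept. It does not remove the point: the article itself names ApoE4 for models whose results it credits to TAS Test, and this conflicts with its own stated use.

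A second reply is that the effect may be small. The Background reports slower hand reactions in cognitively unimpaired ApoE4 carriers, so movement features may share information with genotype, and a refitted model without it could recover part of the loss. That is fair, and the independence assumption may make the illustration too large.

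A third is that ApoE4 is a reasonable covariate when asking what TAS Test adds beyond known risk factors. That also stands, and is why the ApoE4 model should be kept as a secondary result.

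**Conclusion.** The point holds conditionally. If ApoE4 is retained, the Aim 1 cut-offs, sensitivity and specificity, and the Aim 2 multinomial 5-year risks, describe TAS Test plus genotyping and could overstate the home test. At a full-model AUC of 0.90 the illustration gives 0.88–0.90 without ApoE4, and 79–83% sensitivity at 80% specificity against 83%. This rests on the assumed ApoE4-alone AUC and on independent binormal contributions; the documents cannot fix the size.

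Four stronger readings are tempting and are not supported:

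- **That both models definitely contain ApoE4.** The wording is permissive.
- **That ApoE4 in the comparator inflates TAS Test.** It raises the bar.
- **That 60 cases and 290 controls is wrong**, or that the planning AUC is an error because it was estimated "to detect p-tau181 positivity in CSF" while Aim 1 uses plasma. The size is reproduced under conventional assumptions, and the CSF value is openly stated as a planning input.
- **That the loss is much larger.** Assuming an AUC of 0.60 to 0.70 for the null model without ApoE4 takes 0.90 down to 0.87–0.89. But it implies an ApoE4-alone AUC of about 0.66 to 0.73, close to the 0.75 of the whole null model, and nothing in the documents supports that.

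**What to change.** In Statistical analysis, Aim 1 and Aim 2:

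- Make the primary model one limited to inputs available online: TAS Test features, age, sex, years of education and handedness.
- Take the cut-offs, sensitivity, specificity and 5-year risks reported as TAS Test's from that model.
- Report the model with ApoE4 added as a secondary result, labelled TAS Test plus genotype.
- Make any comparison with the null model like for like, with ApoE4 in both models or in neither, so that the difference is what TAS Test adds.

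The sample size need not change on this account. The cost is some wording and one extra model fit per aim, with no new data. The headline accuracy may be slightly lower.

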Potential risks of the study are acknowledged and strategies to mitigate these are now discussed. There is a risk of inadequate recruitment but we will mitigate this by recruiting existing participants in established research cohorts, namely the longitudinal cohorts of THBP, HBA and ISLAND. There is a risk that TAS Test is not sufficiently accurate but we have mitigated this risk by selecting component test items based on evidence of sensitivity to preclinical AD, combining multiple tests to amplify the multivariable model input data [> 10,000 data points], and electing well-established, transparent statistical modelling approaches that reveal the most discriminatory components of motor-cognitive data, allowing further refinement. We have also devised a study protocol that plans to collect a sufficiently large dataset to employ multiple modelling methods, including feature-agnostic deep learning. A further risk is that participants lack a computer camera to provide video-recorded hand movement data, or do not wish to do so; we have mitigated this risk by recruiting participants from studies that have online assessments already, offering the opportunity for participants to attend the clinical research centre in person if preferred, and providing alternate methods (such as keyboard tapping test and mouse click reaction time tests) within TAS Test that collect movement data. It is conceivable that some participants will not want to know their dementia risk and this will hinder selection of participants for the clinical subset assessments, but we have minimised this risk by recruiting from studies that focus on reducing dementia risk, where participants have already undergone multiple tests of dementia risk. It is also important to acknowledge that, as the bulk of this project relies on self-report of known neurological diagnoses, we have limited ability to make distinctions between other neurodegenerative disorders, including other forms of dementia and disorders which are correlated with dementia (for example, Parkinson’s disease). Finally, there are risks around COVID-19 pandemic restrictions limiting recruitment or progress of the study; as most of the study is based around online movement and cognitive tests that can be completed at home, there are likely to be minimal effects and we will be able to collect blood for p-tau181 levels using personal protective equipment or at a later date.

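### The Aim 1 development set is sized by comparing two given AUCs, which does not secure an AUC of 0.90 for a model that must itself be estimated from those 60 cases; no limit on model terms is set

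*Protocol article*

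**What the plan says.** All references are to the protocol article.

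**Sample size, Aim 1.** The comparator comes from a re-analysis of open data: "This showed area under ROC curve (AUC) of 0.75 for a null linear model including age, sex, ApoE4, and years of education". The sizing then reads "To develop the multivariable model, power calculation showed the sample size to compare a screening test with an area under the curve"; the target AUC for that test is above 0.90, the comparator is that null model, and the comparison "would require 60 positive p-tau181 cases and 290 controls". The conclusion is that "we will use 350 in the development dataset (expected 60 [17%] preclinical AD cases"), with 150 people kept back for validation (25 cases expected). No significance level, power or correlation between the two AUCs is given. No number of model terms and no overfitting target is given either.

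**Statistical analysis, Aim 1.** "We will use multiple logistic regression to model the associations between movement features and p-tau181 positivity". Five covariates are named as possible: age, sex, ApoE4, education and handedness. Movement data are to be summarised per participant, models chosen by cross-validation, uncertainty taken from the bootstrap, and the result checked in the held-out 150. Deep learning is secondary. No penalty on the coefficients is mentioned.

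**Aim 2, by contrast.** The sizing names overfitting as a concern, sets a mean absolute prediction error (MAPE) below 0.05, and concludes that "a sample of 300 would be adequate for up to 6 predictors in a parsimonious, statistically determined risk prediction model". Its analysis uses regularizing priors.

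**The concern.** The variance in a two-AUC comparison reflects only the sampling of people whose scores are given. It has no term for estimating coefficients or choosing features. A model fitted to 60 cases therefore performs worse in new people than the best model its features allow, by an amount that grows with the number of terms.

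The article recognises this problem for Aim 2, where it expects 100 cases, and sets a limit of 6 predictors. For Aim 1 it expects 60 cases and offers a longer list of candidates, but sets no limit and names no shrinkage. At stake is how well TAS Test can appear to perform: some movement signal may be lost in the fitting and the test judged weaker than it is.

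**Working it through.** **1. The plan's own figure.** Inputs from the Sample size section: AUC 0.75 v 0.90, 60 cases, 290 controls. Two-sided 5% is assumed. Hanley-McNeil variance: [A(1−A) + (n1−1)(Q1−A²) + (n0−1)(Q2−A²)]/(n1·n0), with Q1 = A/(2−A) and Q2 = 2A²/(1+A).

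- A = 0.75: (0.1875 + 59×0.0375 + 289×0.08036)/17,400 = 0.00147.
- A = 0.90: (0.09 + 59×0.00818 + 289×0.04263)/17,400 = 0.00074.
- Independent AUCs: z = 0.15/√0.00221 = 3.19, so power is 0.89. With correlation 0.5, power is 0.99.
- Cases required if independent: 57 for 80% power (variance pooled under the null), or 63 for 90% (unpooled).

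So 60/290 is a plausible size for comparing two specified AUCs. The unstated inputs mean that it cannot be tied to one power.

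**2. Calibrating the Aim 2 rule.** The article does not print the MAPE formula. The form assumed here is ln(MAPE) = −0.508 − 0.544 ln(n) + 0.259 ln(φ) + 0.504 ln(P), where φ is the outcome fraction and P the number of parameters. With n = 300, φ = 1/3 and P = 6: −0.508 − 3.103 − 0.285 + 0.903 = −2.992, so MAPE = 0.0502. This reproduces the article's 6 predictors.

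**3. The same rule for Aim 1** (n = 350, φ = 60/350).

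- P = 9: −0.508 − 3.187 − 0.457 + 1.107 = −3.044, MAPE 0.048.
- P = 10: MAPE 0.0502 (353 people needed).
- P = 21: MAPE 0.073.

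Hence about 9 parameters.

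**4. Other criteria.** Expected shrinkage of 0.90 gives P = n(S−1) ln(1−R²/S), with Cox-Snell R² derived from the AUC by binormal simulation. At AUC 0.90 (R² = 0.306), P = −35 × ln(1 − 0.306/0.9), about 14. At AUC 0.85, 0.80 and 0.75 it allows 10, 7 and 4. Limiting optimism in Nagelkerke R² to 0.05 allows 12 at AUC 0.90. The range is 4 to 14, and at the article's own 0.90 the MAPE rule is the strictest.

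**5. Candidates listed.** The video section names 9 features plus 2 for antiphase tasks, the keyboard section about 5, and the covariates number 5: 9 + 2 + 5 + 5 = 21. Taken per task, the video section alone gives 9 × 6 = 54, or 59 with covariates. The five covariates would use five of the 9 parameters in step 3.

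**6. Effect on accuracy.** Illustrative simulation: 60 cases, 290 controls, independent normal features, attainable AUC 0.90, performance measured in new data.

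| Parameters, all entered, unpenalised | New-data AUC |
|---|---|
| 9 | 0.89 |
| 20 to 21 | 0.874 to 0.877 |
| 30 | 0.862 to 0.865 |
| 50 | 0.83 to 0.84 |
| 59 | about 0.82 |

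With 59 candidates and a data-driven fit:

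| Method | Sparse signal | Signal spread over many features |
|---|---|---|
| Cross-validated selection | 0.887 | 0.805 |
| Cross-validated elastic net | 0.887 | 0.850 |

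Ridge alone gave 0.859 in the sparse case, below selection.

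**The case against.** The article lists data to be extracted, not terms to be entered. It foresees features chosen by experts, per-participant summaries, optional covariates and cross-validated model selection. Some video features nearly duplicate each other: in a trial of fixed length, tap count is frequency times duration. The article neither names nor excludes a penalty, and an analysis plan that is not shown may settle both the penalty and the candidate list. The held-out 150 will report performance honestly, so no inflated claim would follow.

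Most of this stands, and it rules out several stronger readings.

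- A reader might infer that dozens of terms are planned. No section fixes any number, and the 59-term model is a worst case.
- A reader might infer that an AUC of 0.90 will not be reached, or that power collapses. Both depend on the unstated number of terms and on how the signal is distributed, and the loss is about 0.01 if the model stays near 9 parameters.
- A reader might attribute 60/290 to a particular power, but the inputs for that are not printed.
- The Discussion's remark about "combining multiple tests to amplify the multivariable model input data [> 10,000 data points"] might be read as a count of predictors. It describes raw input volume, and no change to it is needed.

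These points do not supply a basis for the stated sizing. The article gives the two-AUC comparison expressly as the size for developing the model, and it cannot serve that purpose. Cross-validated selection helps when few features carry the signal, but much less when many do.

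**Conclusion.** The point holds in limited form. The two-AUC calculation does not secure an AUC of 0.90 for a model selected and estimated from the same 60 cases, and Aim 1 lacks the parameter limit that Aim 2 has. On the article's own criterion that limit is about 9.

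The likely cost is modest: 0.02 to 0.025 in AUC at 20 to 21 unpenalised terms, and about 0.08 only if some 59 are all entered. These losses assume independent normal features and an attainable AUC of exactly 0.90, so they show scale and are not forecasts. The number 60/290 itself is not shown to be wrong. This is a cheap improvement.

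**What to change.** **Statistical analysis, Aim 1.** Name one of two approaches for the primary model:

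- elastic-net penalised logistic regression, with the penalty tuned by cross-validation within the 350; or
- reduction of the movement data without reference to p-tau181 (for example, one or two summary scores per test section), so that the model has about 9 parameters including covariates.

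Elastic net is preferable to ridge alone because it matched selection in the sparse case and did better than selection when the signal was spread.

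**Sample size, Aim 1.** State that 60 cases and 290 controls is the size for comparing two specified AUCs. Add the parameter limit that 350 people support and the criterion behind it, as is done for Aim 2.

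**Cost.** Analysis wording and standard software, with no extra participants or procedures. Penalised coefficients are less directly interpretable, and their uncertainty must come from the bootstrap already planned.

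### Aim 1 is sized on an AUC comparison with a covariate-only null model, but its analysis never makes that comparison, so the added value of TAS Test would not be shown

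*Protocol article*

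**What the plan says.** **Sample size, Aim 1.** An external open dataset gave the benchmark: "This showed area under ROC curve (AUC) of 0.75 for a null linear model including age, sex, ApoE4, and years of education". The calculation is introduced as one for model development, "To develop the multivariable model, power calculation showed the sample size", and its purpose is a comparison with that benchmark: "power calculation showed the sample size to compare a screening test with an area under the curve (AUC) > 0.90 against the null model". The result is that this "would require 60 positive p-tau181 cases and 290 controls". The 350 participants of the development set are expected to supply those 60 cases. The remaining participants form the hold-out, "150 in the validation dataset (expected 25 [17%] preclinical AD cases"), whose stated job is to test cut-offs taken from the development model.

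**Statistical analysis, Aim 1.** Multiple logistic regression relates movement features to p-tau181 positivity, with deep learning as a secondary route. On adjustment: "Covariates may include age, sex, ApoE4 genotype, years of education, and handedness". Cross-validation is used for model selection, the bootstrap for model uncertainty, and the 150 for independent validation. The stated output is that ROC "curves will be plotted against the positive p-tau181 cut-off to assess the sensitivity and specificity of movement models to identify the preclinical AD stage". No null model is fitted as a comparator, and no difference in AUC is estimated or tested.

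**The concern.** The size and the analysis address different quantities. The size is for a difference between two AUCs; the analysis yields the absolute accuracy of one model.

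This matters because the four null-model variables are all on the list of covariates that may enter the TAS model. By the article's own figure, those four alone reach AUC 0.75 without any finger tapping. If they are in the model, its AUC mixes their contribution with that of TAS Test. If they are left out, the question stays open, because movement features may partly stand in for age. Either way, a reader could not tell what the test adds to facts that cost little or nothing to collect, or to a genotype.

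The figure of 0.75 cannot serve as a fixed yardstick either. It comes from another dataset, with p-tau181 measured in CSF, whereas Aim 1 uses plasma p-tau181 in the THBP and HBA cohorts. The comparator has to be fitted in the Aim 1 participants themselves.

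**Working it through.** **Step 1: sizing against analysis**

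| | Sample size, Aim 1 | Statistical analysis, Aim 1 |
|---|---|---|
| Quantity | AUC > 0.90 v AUC 0.75 | ROC curve, sensitivity, specificity |
| Comparator | age, sex, ApoE4, education | none |
| Role of those variables | they are the null model | optional covariates in the TAS model |

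**Step 2: inputs.** From the article: AUC 0.75 and 0.90 (the bound of the stated > 0.90); 60 cases and 290 controls; 25 cases, hence 150 - 25 = 125 controls, in the hold-out. Not stated, so assumed: alpha 0.05, mainly two-sided; correlation r between the two AUC estimates from 0 to 0.7.

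**Step 3: formulas.** Hanley-McNeil variance for n cases and m controls:

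SE² = [A(1-A) + (n-1)(Q1-A²) + (m-1)(Q2-A²)] / (nm), with Q1 = A/(2-A) and Q2 = 2A²/(1+A).

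- A = 0.75: Q1 = 0.600, Q2 = 0.643.
- A = 0.90: Q1 = 0.818, Q2 = 0.853.
- 60/290: SE = 0.0384 (0.75) and 0.0272 (0.90).
- 25/125: SE = 0.0595 (0.75) and 0.0422 (0.90).

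SE of the difference under the alternative: D1 = √(SE75² + SE90² - 2r·SE75·SE90). Under the null: D0 = SE75·√(2(1-r)).

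- Form A (null variance for the test): power = Φ[(0.15 - 1.96·D0)/D1].
- Form B (alternative variance throughout): power = Φ[0.15/D1 - 1.96].

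**Step 4: the plan's own figure.** With one-sided alpha 0.05, 90% power, r = 0 and form A, the requirement is 60 cases at 290/60 controls per case, which matches the article. With two-sided 0.05 and 80% power it is 57. With r = 0.5, two-sided, it is 29 (80% power) or 38 (90%). So 60/290 is plausible, but it cannot be traced to one set of inputs.

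**Step 5: power for 0.90 v 0.75, two-sided 5%**

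| r | 60/290, A | 60/290, B | 25/125, A | 25/125, B |
|---|---|---|---|---|
| 0 | 82% | 89% | 42% | 54% |
| 0.3 | 94% | 96% | 58% | 68% |
| 0.5 | 98.6% | 99.2% | 74% | 81% |
| 0.6 | 99.6% | 99.8% | 83% | 88% |
| 0.7 | >99.9% | >99.9% | 92% | 94% |

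Example, 25/125, r = 0, form A: D0 = 0.0595 × 1.414 = 0.0841; D1 = √(0.0595² + 0.0422²) = 0.0729; (0.15 - 1.96 × 0.0841)/0.0729 = -0.20; Φ = 42%.

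Against a fixed null of 0.75, which ignores the sampling error of the null model, 25/125 gives 79%.

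**Step 6: precision of what the hold-out is meant to estimate** (Clopper-Pearson, 95%). Sensitivity 20/25 = 80%: 59% to 93%. Sensitivity 21/25 = 84%: 64% to 95%. Specificity 100/125 = 80%: 72% to 87%. These intervals need no assumption about r.

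**The case against.** The strongest reply has four parts.

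- **The target is above 0.90.** A model that only reproduced the covariates, at about 0.75, would visibly fall short. That is true for that extreme. It does not help with results in between, and the analysis section sets no AUC threshold for success.
- **Movement effects would be adjusted.** If covariates enter the logistic regression, the movement terms are adjusted for them, and the ROC curves are described as those of movement models. This weakens the worry but does not remove it. An adjusted association is not a gain in discrimination, and whether the covariates enter is left open.
- **Overfitting is addressed.** The article plans cross-validation, bootstrap and an independent set of 150, and this stands. None of these supplies the missing comparator, and cross-validation is tied to model selection.
- **An article may leave final covariates to the full plan.** That is fair for the covariate list. It is less so for the one contrast that justifies the sample size, when the analysis is described at length and reports something else.

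A reader might also infer that the hold-out breaks the plan's own requirement, with 25 cases where 60 are needed. The article does not support this. It ties 60/290 to model development, meets it there, and gives the 150 another job. The limited hold-out power in the working arises only if the AUC comparison is made on those 150. It also depends on r, and the low end (r = 0) is the least plausible for two models that share covariates in the same people.

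Nor do the documents show the split into 350 and 150 to be wrong. Replacing it with cross-validation over all 500 would be a design preference.

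**Conclusion.** The point holds as a mismatch within the article: Aim 1 is sized on an AUC difference from a covariate-only model, and the Aim 1 analysis neither fits that model as a comparator nor estimates the difference. Followed as written, it could describe the accuracy of a model but not what TAS Test adds. This conclusion rests on the two sections alone and needs no assumption.

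The numerical side is conditional. For 0.90 v 0.75 at two-sided 5%, the development set has at least 82% power at every r examined. That figure does not allow for optimism if models are selected and compared on the same people. Hold-out power runs from 42% to 94% over r = 0 to 0.7 and the two variance forms, so no single value should be printed as fact. None of these figures applies to a contrast without ApoE4, because the article gives no AUC for age, sex and education alone. Separately, the article states no precision for the 25 validation cases, and a sensitivity near 80% would carry an interval about 34 percentage points wide (59% to 93%).

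**What to change.** 1. In the Aim 1 analysis, fit the null covariate model in the same participants. Report the paired difference in AUC (TAS plus covariates minus covariates alone) with a 95% CI.
2. Base it on predictions not optimised on the same data: the 150 held-out participants, cross-validation with feature extraction and selection repeated inside the folds, or both.
3. Report the same contrast without ApoE4, since the intended use is a low-cost pre-screen at home and ApoE4 requires a genotype.
4. In the Sample size section, give the alpha, sidedness, power and correlation behind 60/290, and say that it supports the comparison in the development set only.
5. State the expected precision for 25 validation cases, for example 59% to 93% around 80%. If the AUC difference is to be read from the hold-out, give its power as a range over r.

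The cost is some additional analysis and a less favourable stated precision. No extra participants are needed, and the split of 350 and 150 can stay. The change should be made before the p-tau181 results are modelled.
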